## Methods/design

Here we present our two-phase study, shown in Fig. 1. In phase 1, we aim to have the Visual impairment in Parkinson’s Disease Questionnaire (VIPD-Q) completed by at least 750 PD patients and 250 healthy controls. In phase 2, a subgroup of responders (*n* = 100) will be invited for an extensive neurological and ophthalmological assessment. The study is performed at three study sites (Radboud University Nijmegen Medical Centre, the Netherlands; the Medical University Innsbruck, Austria; and The OLVG hospital Amsterdam, the Netherlands). Each centre obtained local ethical approval (NL58535.091.16;AN2016–0181).The study will be performed in accordance with the Declaration of Helsinki. All participants have to give written informed consent prior to participation. This study is registered in The Dutch trial register: NTR 7663.

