### Phase 1: screening questionnaire

The VIPD-Q was developed by neurologists and ophthalmologists to detect a broad range of ophthalmologic disorders in PD patients. It is based on an extensive literature study, previous questionnaires, and common and disabling visual disorders in both PD patients and healthy older people [2, 11, 13, 15, 17–34]. The questionnaire includes 22 questions on visual problems, plus a standard set of demographic data (Additional file 1: Appendix 1). Answers are given on a 4-point Likert scale ranging from “never have problems” to “daily problems”, without possibility to give a neutral answer. As a second step, we grouped the questions according to the anatomical location of a visual disorder. These domains were agreed upon by a consensus procedure involving three independent ophthalmologists (one from each study site). They were asked to categorize the questions in four domains (Table 1: ocular surface, oculomotor, intra-ocular and optic nerve). Consensus was reached during a meeting with the three ophthalmologists. Six questions could not be categorized in one domain, but rather indicate the involvement of more than one anatomical domain. The VIPD-Q is designed as a patient self-scoring instrument and takes about 20 min to complete.

**Table 1 Tab1:** Domains and corresponding questions with possible diagnosis

Domains	Issues	Possible diagnosis	Question
Ocular surface	lacrimal fluid, eyelids, conjunctiva, cornea	dry eye disease, blepharitis, blepharospasm, conjunctivitis, low eye blink rate,	1: I have blurry vision, when I read or work on a computer. 2: I have a burning sensation or gritty feeling in my eyes. 3: I have mucus/slime or particles in my eyes or eyelids. 4: I have watery eyes.
Intra-ocular	lens, uvea, macula, retina	diabetic retinopathy, macular degeneration, retinal detachment, hypertensive retinopathy, micro-vascular retinopathy, cataract, refraction errors, glaucoma	5: When I read, some letters disappear. 6: Lines that should be straight, appear to be wavy or blurred. 7: I won’t go out alone in the evening or at night because my night vision is insufficient. 8: When I drive at night, the oncoming headlights cause more glare than before.

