Oculomotor	eye movements, binocular cooperation	strabismus, convergence insufficiency, 3rd, 4th and 6th nerve palsies, nystagmus, gaze abnormality	9: Quick movements are hard to follow with my eyes. 10: I have double vision. 11: I can read better with one eye closed. 12: I have trouble with depth perception. I find it hard to say which one of two objects is closer.
Optic nerve	optic nerve disease	opticopathy, glaucoma (Mimics: structural lesion, hemianopsia)	13: Colours seem to be paler than before. 14: I can’t read plain text on a coloured or grey background. 15: I run into objects or people or feel that parts of my visual field are missing. 16. I have problems with rapid changes of light intensity. (For example, driving through a tunnel).

The Visual Impairment in Parkinson’s Questionnaire (VIPD-Q) has been divided in 4 domains as shown above. These domains were agreed upon by a consensus procedure involving three independent ophthalmologists (one from each study site). Six questions of the questionnaire could not be categorized in one domain, but rather indicate the involvement of more than one anatomical domain

The VIPD-Q is both available on paper and online (in English, German and Dutch). We will distribute the questionnaire using different strategies: (1) PD patients visiting the neurologic outpatient clinics at the three study sites (complete the questionnaire on site); (2) PD patients receiving care in one of the participating centres (will receive the questionnaire via post); and (3) PD patients interested in research, having registered on a platform for research and innovation in PD: www.parkinsonnext.nl (will receive the online questionnaire through e-mail). Healthy controls will be recruited by asking partners and family members of participating patients to also complete the questionnaire.

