### Phase 2: neurological and ophthalmological assessment

#### Patient collective and recruitment

From the responders of phase 1, a sample of 100 patients will be invited for a full clinical and ophthalmological assessment. Patients will be selected based on their scores on the VIPD-Q aiming to include 70 patients with and 30 patients without visual impairment, which is operationally defined as patients scoring the highest 30% or the lowest 30% on the screening questionnaire, respectively. Due to personnel capacity, a sample of 30 patients in the Netherlands (10 in the lowest 30% and 20 in the highest 30%) and 70 patients in Austria (20 in the lowest 30% and 50 in the highest 30%) will be selected and invited for the clinical and ophthalmological assessment. The OLVG hospital only participated in phase 1 of this study. Inclusion and exclusion criteria are described in Table 2. Selection will start after at least 250 questionnaires have been completed. (See Fig. 1).

**Table 2 Tab2:** Inclusion and exclusion criteria

Inclusion criteria	Exclusion criteria
Diagnosis of PD according to the UKPDSBB criteria	Hoehn and Yahr Parkinson’s staging score ≥ 4
The patient must be able and willing to give written informed consent	Secondary cause of parkinsonism as detected by history (e.g. drug-induced parkinsonism)
The patient must be willing to participate in all study related activities and visits	Secondary cause of parkinsonism as detected by investigation (e.g. vascular parkinsonism as detected by neuroimaging)
Age of onset Parkinson’s disease > 30 years	Dementia according to DSM-IV
Stable doses of Parkinson medications ≥4 weeks	Major depressive disorder according to DSM-IV
Current age ≥ 60 years	Psychotic disorder(s) according to DSM-IV
	Prior brain surgery (except deep brain stimulation)
	Previous eye surgery (except phacoemulsification for cataract and artificial lenses)
	Blindness in 1 eye
	Medication that influences normal visual function other than PD medication. (Detailed information, please see Additional file 2: Appendix 2)
	Systemic diseases that may cause eye problems (HIV, DM type I, type II if the patient had ophthalmologic therapy and/or abnormalities at last screening)
	Neurodegenerative diseases other than Parkinson’s disease
	History of lesions near the optic chiasm or occipital cortex
	Migraine

Inclusion and exclusion criteria of the Visual Impairment in Parkinson’s Disease study

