
### Statistical analysis plan

95% Confidence intervals, means, standard deviations and frequency distributions will be calculated for all outcomes. Nonparametric variables (age, disease duration, LED, total score VIPD-Q) will be expressed as the median, interquartile range (IQR), minimum, and maximum. To compare groups, we will use the student’s t-test for parametric continuous variables and the Mann-Whitney U test for non-parametric continuous variables. All analyses will be performed with SPSS 22.0 (SPSS Inc., IBM, Chicago, IL, USA).

To address the first study objective (validity of the screening questionnaire), we will compare the results of the VIPD-Q with the ophthalmological assessments using analysis of intraclass correlation coefficient (ICC), with Cohen’s kappa. The results of the ophthalmological assessments will be categorized in visual disorders within the domains of the VIPD-Q (ocular surface, intra- ocular, oculomotor and optic nerve). We hypothesize moderate to good correlation (ICC > 0.5) between the scores on the domains based on the ophthalmological tests and the scores on the domains based on the screening questionnaire. We will also address correlation for the total score. In addition, we will calculate optimal cut-off points of the domains and total score of the VIPD-Q using the receiver operating characteristic (ROC).

For the second and third objective (determine the prevalence and severity of visual problems in PD; impact on clinical functioning), PD patients will be compared with healthy controls using chi-square-tests for categorical values (sex, education, co morbidity, visited ophthalmologist, visual aid, vision changes during the day, difficulties with daily activities, impact on quality of life) or Mann-Whitney U test for non-parametric continuous variables (age, total score VIPD-Q, score per domain). Furthermore, the relationship between falling, disease duration, MDS-UPDRS, hand-eye dexterity, gait and balance tests, and visual problems will be assessed using multiple linear regression analysis.

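### The comparison of PD patients with partner and family controls uses unadjusted tests, so any age or sex imbalance can produce or mask a difference

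*Protocol article*

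**What the plan says.** The article's section Statistical analysis plan sets the group comparison for the second and third objectives. It states that "PD patients will be compared with healthy controls using chi-square-tests for categorical values", and the items listed for that test are "sex, education, co morbidity, visited ophthalmologist, visual aid, vision changes during the day, difficulties with daily activities, impact on quality of life". For the rest it names the "Mann-Whitney U test for non-parametric continuous variables (age, total score VIPD-Q, score per domain"). Age and sex therefore stand in the same lists as the outcomes. They are tested for a difference between groups and are not used as covariates or strata.

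The source of the controls is given under Phase 1: screening questionnaire: "Healthy controls will be recruited by asking partners and family members of participating patients to also complete the questionnaire". The target in Methods/design is to have the questionnaire "completed by at least 750 PD patients and 250 healthy controls".

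Only one multivariable model is described: "the relationship between falling, disease duration, MDS-UPDRS, hand-eye dexterity, gait and balance tests, and visual problems will be assessed using multiple linear regression analysis". Disease duration and MDS-UPDRS are PD measures and no PD-versus-control term is named, so this model does not adjust the group comparison.

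**The concern.** Controls found through the patients are not a random or matched sample. Partners may differ from patients in sex, and family members can be of the same generation, older or younger. The entry "Current age ≥ 60 years" is in Table 2, which the article cites for selecting phase 2 patients. No age limit is stated for the phase 1 controls.

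Age plausibly matters for the outcome. The article says the questionnaire draws on "common and disabling visual disorders in both PD patients and healthy older people", and Table 1 links items to cataract, macular degeneration and glaucoma.

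Chi-square and Mann-Whitney tests take no covariates. If the groups differ in age or sex, and scores depend on either, the comparison mixes that difference with PD. Testing age and sex between groups would show an imbalance but would not remove it from the VIPD-Q comparison. At stake is whether a reported difference, or the absence of one, in scores, daily-activity items or quality-of-life items can be read as related to PD.

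**Working it through.** The article states no alpha, power, effect size or SD for the group comparison, so there is no stated calculation to reproduce. The check asks how far a plausible imbalance would shift the planned tests.

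**Inputs from the article:** 750 patients and 250 controls; Mann-Whitney U for total and domain scores.

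**Assumptions, not in the article:** two-sided alpha 0.05; age SD 9 years in each group; correlation r between age and score of 0.1 to 0.3; controls younger by 2 to 8 years; no true PD effect.

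**Step 1. Precision.** In SD units of the score, SE = √(1/750 + 1/250) = √0.00533 = 0.073. By the usual two-sample calculation the design has about 80% power for a difference of 0.205 SD, so a bias of 0.1 to 0.2 SD is comparable with the effects it can detect.

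**Step 2. Bias from age.** Bias in SD = r × gap / 9. At r = 0.2 and a 5-year gap this is 0.2 × 5 / 9 = 0.111.

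**Step 3. False-positive rate.** Let z = (bias / SE) × √(3/π), where √(3/π) = 0.977 allows for the efficiency of the Mann-Whitney test under normality. Then P(significant) = 1 − Φ(1.96 − z) + Φ(−1.96 − z). For the example, z = (0.111 / 0.073) × 0.977 = 1.49 and P = 0.32.

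| r | 2-year gap | 5-year gap | 8-year gap |
|---|---|---|---|
| 0.1 | 6% | 12% | 22% |
| 0.2 | 9% | 32% | 66% |
| 0.3 | 15% | 61% | 95% |

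Simulation of 2000 data sets per scenario agrees: at r = 0.2 the Mann-Whitney rates were 10%, 33% and 66%. With no age gap and no sex difference the rate was 5%.

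**Step 4. Sex alone.** Bias in SD = sex effect × difference in the proportion of women. Assume 60% men among patients, 40% among controls, and women scoring 0.2 to 0.3 SD higher. The bias is 0.04 to 0.06 SD and the simulated false-positive rate 8% to 13%. At 65% and 35% men with a 0.3 SD sex effect it is 24%.

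**Step 5. Masking.** The bias can also work against a true effect. For an assumed true PD effect of 0.2 SD, simulated Mann-Whitney power is 76% with balanced groups. It falls to 45% with the 60/40 sex split and a 0.3 SD sex effect, and to 22% if controls are 5 years older at r = 0.2. With controls 5 years younger it rises to 99%, which is bias and not information.

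**Step 6. After adjustment.** Linear regression on group, age and sex brought the false-positive rate to 4.5% to 6.0% in every null scenario, and power for the 0.2 SD effect to 76% to 79% throughout.

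**Step 7. Related patients and controls.** Take 250 patient-relative pairs with an assumed within-pair correlation of 0.2. The variance of the difference is 0.00533 − 2 × 0.2 / 750 = 0.0048, so an unpaired test is slightly conservative (about 4%). If each participating family gave two controls, with the same correlation, the variance is 1/750 + 1.2/250 − 0.4/750 = 0.0056, an SE about 2.5% larger and a rate just under 6%.

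**The case against.** The strongest reply is that the affected comparison is not the centre of the study. Objective 2, as worded in the Abstract and Background, is the prevalence and severity of visual problems in PD. That is estimated within patients and does not depend on controls. Objective 1, the validation by ICC, kappa and ROC, uses no controls, and neither does the regression on falls, gait and balance. This stands and limits the severity. It does not remove the point, because the analysis section makes the control comparison the stated analysis for objectives 2 and 3.

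A reader might infer that age and sex are bound to differ. The documents do not support that. They give no age or sex distribution and no split between partners and other relatives. Partners may be close to patients in age, and siblings and children could pull the mean either way. At a gap of 0 to 2 years the rate stays near nominal (5% to 9% at r = 0.2), and age and sex effects can partly cancel. This stands: the claim is that imbalance can bias the comparison, not that it will.

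A reader might also infer that recruiting relatives invalidates the tests through dependence. Step 7 shows a small effect, in either direction.

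Finally, a journal article condenses a longer protocol, which could hold a covariate set. But the article does not leave the method open. It names tests that cannot take covariates, so this is a stated choice and not a missing detail. The planned comparison of age, sex and comorbidity would let readers see an imbalance, but not correct for it.

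**Conclusion.** The point holds as a should-fix. The method stated for comparing PD patients with controls has no protection against confounding by age and sex, and the control source gives no assurance of balance. The direction is unknown: younger controls would inflate a PD effect if complaints rise with age, while older controls would hide one, as would more women among controls if women report more problems.

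The size depends on the assumptions listed above. It runs from close to nominal for a 2-year gap (6% to 15% over the correlations tried) to a majority of false positives for an 8-year gap at correlation 0.2. These figures illustrate sensitivity and do not predict this study's error rate. Reading the concern as undermining the study's main results would go too far, since the PD prevalence estimates and the questionnaire validation are untouched.

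**What to change.** State that the main PD-versus-control estimate for each VIPD-Q outcome comes from a regression on PD status with age and sex as prespecified covariates: ordinal or linear regression for total and domain scores, logistic regression for binary items. Report adjusted differences or odds ratios with 95% confidence intervals. Keep the chi-square and Mann-Whitney tests as description. Family-clustered standard errors are an optional minor refinement where the link between patient and relative is recorded.

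The cost is a change of wording and a little analysis. The plan already lists age and sex for both groups, so no new data are needed. Phase 1 recruitment ended in August 2018 according to Trial status, so matching at recruitment is no longer possible and adjustment in the analysis is the practical remedy.

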The current multicentre observational, cross-sectional VIP study: “Visual Impairment in Parkinson’s disease” is designed to promote knowledge about and recognition of symptoms, signs and causes of disturbed vision in people with PD. Our specific goals are to: (1) validate a screening questionnaire that aims to identify PD patients who should be referred to an ophthalmologist for further assessment; (2) determine the prevalence and severity of visual problems in PD; (3) study the impact of ophthalmologic disorders on clinical functioning (in particular on gait and balance control); and (4) explore treatment options for ophthalmologic disorders in PD, as a basis for future guideline development.

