#### Gait and balance

Performance tests measuring different aspects of gait and balance will be performed. Walking velocity will be tested under single and dual-tasking conditions [39, 40]. The patients will be instructed to walk a distance of 4 m at self-preferred speed. The required number of steps will be reported as outcome. The Timed-Up-and-Go-test (TUG) measures the basic functional mobility [41]. Freezing of Gait (FOG) is assessed by letting the patient make a 360° turn with small steps (approximately 25% of their own preferred step length) and walking fast with short steps [42]. To test axial symptoms, tandem gait at a self-preferred speed is recorded for at least 10 consecutive steps without a visual guiding line [43]. The Single Leg Stance test (SLS) will be used to test static balance and postural instability [43–46]. Finally, postural stability will be recorded by the Pull-Test (item 3.12 MDS-UPDRS).

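### The clinical-impact regression lists no age and names no dependent variable, so in a sample taken from the VIPD-Q extremes it can mix age with vision and, in one direction, inflate slopes

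*Protocol article*

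**What the plan says.** In the protocol article, the Background sets the third goal: to "study the impact of ophthalmologic disorders on clinical functioning (in particular on gait and balance control"). The Statistical analysis plan section gives the regression for it in one sentence: "the relationship between falling, disease duration, MDS-UPDRS, hand-eye dexterity, gait and balance tests, and visual problems will be assessed using multiple linear regression analysis". Nothing more is said about which variable is dependent, how many models there are, or whether the visual measure is the questionnaire score or the examination result.

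The same section uses age for description, "Nonparametric variables (age, disease duration, LED, total score VIPD-Q) will be expressed as the median", and for the comparison of patients with controls, but does not name it for the regression.

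The MDS-UPDRS, gait and dexterity tests belong to phase 2. Under Patient collective and recruitment, those 100 patients are "patients scoring the highest 30% or the lowest 30% on the screening questionnaire, respectively", 70 from the top and 30 from the bottom. Table 2 requires "Current age ≥ 60 years" and sets no upper limit. Under Gait and balance, "postural stability will be recorded by the Pull-Test (item 3.12 MDS-UPDRS").

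**The concern.** Three features of the sentence act together.

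- **Age.** The list has disease duration but not age. The article itself ties vision to age: the questionnaire draws on disorders seen in healthy older people, and the contrast threshold is specific to people over 60. Age plausibly worsens gait as well. An analysis confined to the list can then credit vision with what is partly age.
- **Direction.** The sample is selected on the VIPD-Q. Regressing that score on function gives a distorted slope; regressing function on the score does not.
- **Model type.** The Background and Discussion treat falls as a consequence of poor vision, so falling is a natural outcome. A yes/no or count variable does not suit a linear model.

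At stake is the answer to the third goal, which is meant to show how much visual disorders matter for gait and balance.

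**Working it through.** **Inputs.** From the article: n = 100, 70 high and 30 low scorers, tails of 30%. The allocation adds up: 10 + 20 = 30 in the Netherlands, 20 + 50 = 70 in Austria; low 10 + 20 = 30, high 20 + 50 = 70. The article gives no power, effect size or correlation for this analysis, so there is no planned figure to reproduce. Assumed: the age correlations, the true slope, a two-sided 5% test and a normal score.

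**Step 1: age left out.** With no direct effect and no other covariate, spurious r = r(age, vision) × r(age, function). The approximate rejection rate in an unselected sample of 100 comes from z = atanh(r) × √97. For 0.4: r = 0.4 × 0.4 = 0.16, z = 1.59, and P = 1 − Φ(1.96 − 1.59) = 0.36. The simulation drew 100 of 750 patients from the score extremes at 70:30, in 2,000 runs, with the score as the visual measure.

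| Assumed age correlation with both | Spurious r | Rejection, unselected | Rejection, simulated extremes | Simulated, age included |
|---|---|---|---|---|
| 0.2 | 0.04 | 7% | not run | not run |
| 0.3 | 0.09 | 14% | 18–19% | 5% |
| 0.4 | 0.16 | 36% | 46–47% | 5% |
| 0.5 | 0.25 | 71% | 85–87% | 5% |

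Sampling the extremes raises the rates because it stretches the score. Disease duration and MDS-UPDRS are in neither calculation and could absorb part of the age effect.

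**Step 2: selection on the score.** For a standard normal score the mean of a 30% tail is ±1.159, with cut point 0.524.

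- Mean in the sample: (0.7 − 0.3) × 1.159 = 0.464.
- Mean square: 1 + 0.524 × 1.159 = 1.608.
- Variance ratio: k = 1.608 − 0.464² = 1.393.

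*Score as dependent variable:* slope = r·k / (1 − r² + k·r²). For r = 0.30: 0.418 / (0.91 + 0.125) = 0.404, or +35%. Over true slopes of 0.1 to 0.5 the inflation runs from +39% to +27%.

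*Score as exposure:* the unstandardised slope stays at 0.30 (simulation 0.298). The correlation, which is also the standardised coefficient with one predictor, becomes 0.30 × √1.393 / √1.035 = 0.348, or +16%. R² goes from 0.09 to 0.121.

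*Examination result as dependent variable:* if it correlates 0.3, 0.5 or 0.7 with the score, and function relates to the score only through it, the slope inflation is 3%, 9% or 17%.

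Selection alone creates nothing from nothing: a true zero stays zero, with rejection near 5%.

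**Step 3: model type.** The article does not define how falling is recorded. A binary or count variable is acceptable as a predictor in linear regression. It becomes a problem as the dependent variable, which is the role the third goal suggests.

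**The case against.** The strongest reply is that a journal article need not print its full covariate set. The sentence names relationships under study, and silence on age is not a decision to exclude it. That stands as a limit: nobody can say from this article that age will be left out. But the sentence is not silent on variables. It names disease duration and MDS-UPDRS beside a fixed method, and the same section assigns age other uses.

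Second, the third goal reads with function as the outcome, and then the unstandardised slope is not inflated. This is largely right. The list still leaves doubt, because disease duration cannot be an outcome of vision yet stands in the same series as the functional tests.

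Third, the +35% needs the VIPD-Q score as dependent variable and a normal distribution, while the plan classes that score as nonparametric. This stands, and the figure is an example only. Nor can that inflation and the unsuitable model for falls occur in the same model, since each needs a different dependent variable.

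A reader might also infer one joint regression in which the functional tests adjust each other away. The text gives no number of models and equally fits one per outcome. Double entry of the pull test is likewise only an inference: Table 3 does not list it among the gait and balance tests, and the regression sentence does not name it.

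**Conclusion.** The point holds as a weakness in what the sentence fixes: a linear method and a variable list without age or a stated direction, for a sample drawn from the score extremes. Run on that list, the analysis can report an association that is partly age. Its size depends on age correlations that the article does not give. It is negligible at 0.2 and serious at 0.4 or more, before any share taken up by the listed covariates.

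A reader might conclude that the reported associations will be confounded and inflated. The article does not support that. Confounding is plausible but unquantified, and slope inflation arises only if the score, or to a lesser degree a correlate of it, is the dependent variable. With the score as exposure, what remains is inflation of correlations, standardised coefficients and R².

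**What to change.** Replace the regression sentence with a statement that:

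- each functional measure (gait, balance, dexterity, falling) is the dependent variable in its own model, and the visual measure, named as score or examination result, is the exposure;
- age is a covariate beside disease duration and MDS-UPDRS;
- falling, when it is the outcome, is analysed by a logistic model if recorded as yes/no or a count model if recorded as a number;
- item 3.12 is left out of the MDS-UPDRS covariate if the pull test is the outcome;
- unstandardised coefficients are the main result, and any correlation, standardised coefficient or R² is labelled as coming from an extreme-group sample.

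No new data are needed, since age is already collected. The cost is wording, analysis time and a few degrees of freedom at n = 100. In the simulated settings, adding age brought false rejection back to about 5%.
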